## Abstract

*Taenia solium* diagnosis is challenging as trained personnel, good diagnostic tools, and infrastructure is lacking in resource-poor areas. This paper aims to describe the study trial design adopted to evaluate a newly developed rapid point-of-care test that simultaneously detects taeniosis and neurocysticercosis (TS POC) in three district hospitals in Tanzania. The two-stage design included three types of patients: patients with specific neurological signs and symptoms (group 1); patients with complaints compatible with intestinal worm infections (group 2); patients with other symptom(s) (group 3). For group 1, all patients were tested using the TS POC test (stage 1), after which all positive, and a subset of negative, patients were selected for laboratory reference tests, clinical examination, and a brain computed tomography (CT) scan (stage 2). For groups 2 and 3, a similar design was adopted, but clinical examination and a brain CT scan (stage 2) were only performed in patients who were TS POC test-positive for cysticercosis. Due to the lack of a gold standard, a Bayesian approach was used to determine test accuracy for taeniosis and cysticercosis. For neurocysticercosis, a composite case definition was used as the reference standard. If successful, this study will help the future developments (commercialization and implementation) of the rapid test and improve patient management and disease prevention.

## 1. Introduction

*Taenia solium* is a neglected zoonotic parasite contributing to the significant health and economic burden in affected areas of low- and middle-income countries (LMIC) [1].

In Tanzania, several projects on *T. solium* cysticercosis have been conducted and provided evidence of the parasite presence in several regions of the country [2]. Based on antigen enzyme-linked immunosorbent assay (Ag-ELISA) and antibody (Ab)-ELISA, the prevalence of human cysticercosis (CC) was 16.7% and 45.3%, respectively, in the Songwe region, southern Tanzania in 2009. In the same area, the prevalence of taeniosis (T) was estimated to be 5.2% using copro-Ag ELISA [3]. In the Mbulu district, northern Tanzania, a hospital-based brain computed tomography (CT) scan study indicated that almost 20% of people with epilepsy suffered from neurocysticercosis (NCC) [4,5].

At the district hospital level, the diagnosis of tapeworms can be performed using microscopy, but has a low sensitivity and fails to differentiate *Taenia* spp. Other methods, such as the copro-antigen ELISA, the recombinant antigen-based enzyme-linked immunoelectrotransfer blot (EITB), and polymerase chain reaction (PCR) techniques are available but also have limitations in their performance, and are used only in research settings as laboratories at the district hospital level in Tanzania lack equipment, adequately trained experts, and infrastructure [6]. Moreover, differential diagnosis and the stigma associated with epilepsy further contribute to the challenges that district hospitals face [7].

To standardize the diagnosis of NCC, Del Brutto et al. [8] formulated a set of criteria based on neuroimaging, assisted by serological, clinical, and epidemiological results. Neuroimaging is possible using CT and/or magnetic resonance imaging (MRI). For serology, the lentil lectin-bound glycoproteins-enzyme-linked immunoelectrotransfer blot (LLGP-EITB) is the test of choice [8,9]. In resource-poor areas, this is problematic as access to neuroimaging is very limited, trained neurologists are scarce, and the LLGP-EITB, though considered as having high specificity and sensitivity [10], is expensive and in a format not applicable/available in most local laboratories. Therefore, disease diagnosis in resource-poor areas outside a research setting is hampered by the lack of good tools and skilled personnel, as well as the high costs. 

To limit these challenges, a user-friendly, rapid, cheap *T. solium* point-of-care test (TS POC) was developed by the Centre for Disease Control and Prevention, Atlanta, USA, in collaboration with the Klinikum rechts der Isar, Technical University of Munich, Germany. 

The main objective of the SOLID project (“Evaluation of an antibody-detecting point-of-care test for the diagnosis of *Taenia solium* taeniosis and neurocysticercosis in communities and primary care settings of highly endemic, resource-poor areas in Tanzania and Zambia, including the training of—and technology transfer to the Regional Reference Laboratory and health centers”) was to evaluate the sensitivity/specificity and ease of use of the TS POC test for the detection of *T. solium* T and NCC in resource-poor, highly endemic areas in sub-Saharan Africa. The study in Zambia was conducted in a community-based setting and its design was published elsewhere [11]. This paper focuses on the design of the diagnostic accuracy evaluation of the TS POC test at the district hospital level in Tanzania. 

## 2. Materials and Methods

### 2.1. TS POC Test

A detailed description of the TS POC test is presented in [11]. To summarize, the TS POC test is an antibody-detecting prototype developed by a team of researchers from the USA and Germany. The TS POC test consists of a double-strip cassette that holds one strip for the detection of antibodies against the adult stage (using the recombinant T antigen rES33), and one to detect antibodies against the larval stage of the parasite (using the recombinant CC antigen rT24H) [12,13]. Each strip has one test line, one control line, and a separate port for the sample application, enabling the simultaneous detection of T and CC antibodies. 

For the TS POC test evaluation in Tanzania, 3000 tests were produced at CDC Atlanta in collaboration with Arista Biologicals Inc, Allentown, PA, USA. 

Details on how the TS POC test was performed and read can be found in [14]. In essence, two times 20 micro-liters of blood are collected from a fingertip using a micropipette and placed on the sample well for T and CC, respectively. Immediately after, the chase buffer is applied, and as soon as the flow commences the timer is set for 20 min (Figure 1). The TS POC test is read by two independent readers (two-factorial design), and in the case of a disagreement, a third reader intervenes. A result card is used to report the results which are subsequently entered in electronic case report forms (eCRFs). In the case of an invalid result (e.g., no flow, or control line missing), the test is repeated once.

### 2.2. Study Design, Recruitment, and Eligibility

To evaluate the diagnostic performance of the TS POC test for the detection of T, CC, and NCC, a prospective, two-stage, multicenter study was conducted. The TS POC test was evaluated at the stage where it may be implemented in practice, being patients attending district hospitals in *T. solium*-endemic areas. Since the accuracy of the test was likely to vary across subgroups of patients [15], the study was performed on three groups of patients, namely patients with specific neurological signs and symptoms (epilepsy and/or severe progressive chronic headache) (group 1); patients with complaints compatible with intestinal worm infections (group 2); patients with other symptom(s) (group 3). To get a representative sample for the studied populations, subjects for groups 1 and 2 were consecutively recruited, while for group 3, only every tenth patient was included if eligibility criteria were met. Recruitment took place between December 2017 and February 2020. 

Patients of group 1 were recruited from the mental health ward or the outpatient department while patients belonging to groups 2 and 3 were recruited from the outpatient department only. To be included, patients had to be ten years old or above and willing and able to participate in all aspects of the study (including providing blood and stool samples, undergoing a clinical examination, and a brain CT scan, if necessary), willing and able to provide written informed consent (assent for minors with consent from a parent or a legally authorized representative), living in the study area for the past three months and planning to stay in the same area throughout the study period. Pregnant women and patients suffering from severe health conditions needing in-patient care were excluded from the study. 

To be eligible for inclusion in group 1, patients needed to present to the mental health ward or outpatient department with on-going symptoms of severe progressive chronic headache impeding their daily activities without fever and signs of cerebral infection or other obvious causes; and/or they should have a history of one or more epileptic seizures without obvious causes. Participants meeting any of the following criteria were not enrolled in the study: less than ten years of age; acute febrile illness; fever and signs and symptoms for middle ear infection; signs and symptoms of meningitis; neck muscle pain and stiffness; a history of stroke with neurological focal deficit; a history of psychiatric problems.

To be eligible for inclusion in group 2, patients had to present at the outpatient department with intestinal complaints suggestive of an intestinal worm infection (diarrhea and/or abdominal pain/discomfort for more than two weeks and/or a recent history of worm expulsion). For group 3, eligible patients with any other symptom(s) not immediately linked with intestinal worm infections or symptoms described for group 1 were also recruited from the outpatient department.

### 2.3. Study Objectives and Outcomes

The primary objective of the study was to assess the sensitivity and specificity of the TS POC test for the diagnosis of each of the disease presentations (T, CC, and NCC). Due to the lack of a gold standard, three different reference tests were used for the detection of T and CC, respectively (Table 1). The diagnostic accuracy of the TS POC test for the detection of T was determined against two stool-based reference methods (copro antigen ELISA and copro PCR) and a serological test (immunoblot using the recombinant protein rES33). For CC, the reference methods were the EITB-LLGP, rT24H immunoblot, and the B158/B60 monoclonal antibody-based serum antigen ELISA. For NCC, a composite case definition was used as the gold standard based on Del Brutto’s criteria [8]. An overview of the different reference tests included is given in Table 1, and a description of the tests is presented in Section 2.6.

### 2.4. Study Area

The study was conducted in three rural district hospitals in the Songwe and Mbeya regions, Tanzania. District hospitals were included based on the following eligibility criteria: (i) presence of a mental health ward; (ii) proximity to an area where T and NCC were prevalent; (iii) closeness to the Mbeya Radiology Centre equipped with a CT scanner. The three district hospitals in Mbozi (Vwawa), in rural Mbeya (Ifisi), and in Rungwe (Tukuyu) were included (Figure 2).

### 2.5. Study Workflow

After enrollment, patients were subjected to the TS POC test, and based on its results, a subset of participants was subjected to several reference tests, clinical examination, and CT scanning of the brain. Per hospital, approximately one-third of the required sample size was enrolled (see Section 2.11). The study design flow for group 1 is visualized in Figure 3, while Figure 4 shows the study design flow for groups 2 and 3.

### 2.6. Reference Sample Collection, Processing, and Analysis 

Sample collection, processing, shipment, and analysis were the same as for the SOLID project community-based study in Zambia [11]. To summarize, 3 mL of venous blood was collected, and the serum was stored at −20 °C until reference testing using the LLGP-EITB, recombinant immunoblots (rES33 and rT24H), and Ag ELISA. Stool samples were stored at room temperature in 10% formalin for copro-Ag-ELISA, and 70% ethanol for copro PCR. 

The samples were shipped and analyzed in Belgium. Most analyses were performed at the Institute of Tropical Medicine in Antwerp, Belgium, with a 20 percent subset of samples analyzed at Ghent University, Belgium, for quality control. Only the serum samples for the Ag ELISA were fully analyzed at Ghent University, with a 20 percent subset of samples analyzed at the Institute of Tropical Medicine in Antwerp.

In short, the LLGP-EITB was performed as described previously [10,16] with a few modifications. The LLGP-EITB strip was considered positive if at least one out of seven bands were visible. For the recombinant strips, rES33 and rT24H lines for T and CC were combined in one strip. All strips were provided by CDC. The B158/B60 serum antigen ELISA was used as previously described [17]. For the Copro-Ag-ELISA, the procedure was performed as reported previously by [18] and modified by [19]. DNA extraction of stool samples (200 µL in 70% ethanol) was carried out using the QIAmp^®^ fast DNA stool mini kit (Qiagen, Hilden, Germany) according to the manufacturer’s instructions. DNA was stored at −20 °C until use. The copro PCR was performed according to [20] with some modifications. A sample was only considered positive if *T. solium* DNA was detected in the sample.

### 2.7. Clinical Follow-Up, CT Scans, and Patient Management

A procedure as described for the community-based study in Zambia was followed [11]. For group 1, all patients were seen by a doctor (Figure 2) who performed a neurological examination, while for groups 2 and 3 (Figure 3) only study participants TS POC CC-positive were seen by a study doctor. Appropriate eCRFs were used to record patients’ personal and clinical data according to principles of good clinical practices. After the neurological examination, including past and current medical history, a cerebral CT scan with and without contrast was taken. Contrast was used only if there were no clinical contraindications. If two or more months between the initial TS POC test result and the CT scan elapsed, a new TS POC test was performed using only the strip for CC.

The CT scan results were read independently by the senior project neuroradiologist and an NCC expert. For each CT scan, the number, location, and stage of the lesion were recorded. In the case of a discrepancy, a third independent reviewer adjudicated the CT diagnosis. The final NCC diagnosis was determined according to the 2017 criteria of [8]. These were based on clinical symptoms, neuroimaging, the detection of antibodies and antigens in serum, and epidemiological considerations corresponding to absolute, major, and minor criteria and resulting in the definite and probable diagnosis of NCC. An absolute neuroimaging criterion for NCC was at least one cystic lesion showing the scolex. Major neuroimaging criteria were cystic lesions without scolex, single or multiple rings, or nodular enhancing lesions, multilobulated cystic lesions in the subarachnoid space, and parenchymal brain calcifications. Hydrocephalus or abnormal enhancement of basal leptomeninges were categorized as minor neuroimaging criteria. Four different stages of lesions were defined: vesicular, colloidal vesicular, granular nodular, and nodular calcified. The first three were considered as active NCC lesions and the last was defined as an inactive NCC lesion [8]. 

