### 2.11. Sample Size and Statistical Analysis

The sample size for group 1 was calculated to obtain the desired half-width of 5% around the 95% confidence interval for sensitivity and specificity [22]. Assuming a sensitivity of 93%, a specificity of 99% [11], and a prevalence of NCC of 20%, 500 participants were required. To account for losses, 20% were added to this number. The final sample size for group 1 was set at 600.

Since the prevalence of T in the study population was unknown, the sample size for groups 2 and 3 was calculated for different plausible values, ranging between 3% and 10%. Assuming a sensitivity of 82%, a specificity of 81%, and the desired precision of 10%, 1890 participants were required. To account for 5% contingencies, the final sample size was rounded to 2000 patients.

The sensitivity and specificity of the TS POC test for the detection of T, CC, and NCC were determined relative to the reference tests as shown in Table 1, for each of the three study groups. Weighting was used to correct for the study design (a subset of T-CC that is selected for sampling/clinical examination). The positive and negative predictive values were also determined.

For T and CC, the diagnostic sensitivity and specificity of the TS POC test were estimated using a Bayesian approach as described previously [23]. For the evaluation of the TS POC test performance for NCC, sensitivity and specificity were computed by cross-tabulating POC results with those of the final NCC diagnosis. More details can be found in [11].

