**Figure 3 diagnostics-11-01528-f003:**
[figure not shown]
Flow of the diagnostic accuracy study in Tanzania for patients attending the mental health ward or outpatient department of district hospitals with on-going symptoms of severe progressive chronic headache impeding their daily activities without fever and signs of cerebral infection or other obvious causes; and/or a history of one or more epileptic seizures without obvious causes (group 1). In this two-stage design, all patients were tested using the TS POC test (=index test; stage 1), after which all positive, and a subset of negative, patients were selected for different reference tests, clinical examination, and a brain CT scan (stage 2).

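### Group 1 verification is described in two ways, and the 500 patients give a 5-point half-width for NCC sensitivity only if every evaluable patient has the NCC reference diagnosis

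*Protocol article*

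**What the plan says.** **Section 2.7** states: "For group 1, all patients were seen by a doctor (Figure 2) who performed a neurological examination". It contrasts this with groups 2 and 3, where only patients positive on the CC strip saw a study doctor. It then says that a cerebral CT was taken after the examination, without naming a group or a subset.

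**The Figure 3 caption**, which describes the group 1 flow, states: "all positive, and a subset of negative, patients were selected for different reference tests, clinical examination, and a brain CT scan (stage 2". The abstract gives the same rule for group 1.

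**Section 2.5** says of the study as a whole, on the basis of the POC result: "a subset of participants was subjected to several reference tests, clinical examination, and CT scanning of the brain".

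**Section 2.11** sizes group 1 for a "desired half-width of 5% around the 95% confidence interval for sensitivity and specificity". The inputs and result are: "Assuming a sensitivity of 93%, a specificity of 99% [11], and a prevalence of NCC of 20%, 500 participants were required". Then: "To account for losses, 20% were added to this number", and "The final sample size for group 1 was set at 600". The same section says that weighting corrects for selecting a subset for sampling and clinical examination, and that NCC accuracy comes from cross-tabulating the POC result with the final NCC diagnosis.

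**The concern.** The abstract and the Figure 3 caption list the clinical examination as a stage 2 procedure that only some POC-negative patients in group 1 reach. Section 2.7 gives it to all of group 1. As written, both cannot describe the same study.

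This matters for more than wording. Sensitivity for NCC depends on how many NCC cases the test missed, and those cases lie among the POC-negatives. If only a fraction of the negatives is examined and scanned, the missed cases are estimated from a small sample and scaled up, and the interval widens. A sample size that treats every patient as verified then promises more precision for sensitivity than the design can give.

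**Working it through.** **Inputs.** From Section 2.11: sensitivity (Se) 0.93, specificity (Sp) 0.99, NCC prevalence 0.20, half-width d = 0.05, 95% interval (z = 1.96), N = 500, final N = 600. Assumed: f, the fraction of POC-negatives verified, shown over a range. POC-positive and POC-negative here refer to the CC strip, which is the strip evaluated for NCC.

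**Step 1: reproduce the plan's figure.**
- Sensitivity: z²·Se(1−Se)/(d²·prevalence) = 1.96² × 0.93 × 0.07 / (0.05² × 0.20) = 500.2, which matches the stated 500.
- Specificity: 1.96² × 0.99 × 0.01 / (0.05² × 0.80) = 19.0, so 20 patients. Sensitivity drives the size.
- Allowance: 500 × 1.2 = 600. With the 2000 for groups 2 and 3, this gives the 2600 patients named in the Discussion. The 600 is therefore an enrolment figure, not a count of verified patients.

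The formula counts all 500 × 0.20 = 100 NCC cases as observed, so it assumes that every evaluable patient has the reference diagnosis.

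**Step 2: expected table at 500.**
- POC-positive: 500 × (0.93 × 0.20 + 0.01 × 0.80) = 97, of whom 93 have NCC.
- POC-negative: 500 − 97 = 403, of whom 500 × 0.20 × 0.07 = 7 have NCC.

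**Step 3: half-width when all 97 positives and a fraction f of the 403 negatives are verified.** The variance of logit(Se), for the estimator weighted by the inverse sampling fraction (Begg-Greenes), has three terms:
- share testing positive: 1/(500 × 0.194 × 0.806) = 0.0128
- NCC among positives: (4/97)/93 = 0.0004
- NCC among negatives: (396/403)/(7f) = 0.1404/f

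Half-width = 1.96 × 0.93 × 0.07 × √(0.0132 + 0.1404/f).

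| f (assumed) | Formula, N = 500 | Simulation, N = 500 | Formula, N = 600, no losses |
|---|---|---|---|
| 1 | 5.0 | 5.0 | 4.6 |
| 0.75 | 5.7 | 5.7 | 5.2 |
| 0.50 | 6.9 | 6.9 | 6.3 |
| 0.25 | 9.7 | 9.5 | 8.8 |
| 0.10 | 15.2 | 14.3 | 13.9 |

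Values are percentage points; the simulated half-width is 1.96 × the standard deviation of the estimates. The formula is rough at small f. At f = 0.10, about 40 negatives are verified and 0.7 NCC cases are expected among them.

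**Step 4: where 5 points is still met.** At 500, f must be about 1. At 600 with no losses, the bracket in Step 3 may be up to (0.05/0.1276)² × 600/500 = 0.184, so f ≥ 0.1404/(0.184 − 0.0132) ≈ 0.82. For a 5-point half-width the evaluable N would be about 958 at f = 0.50, 1872 at f = 0.25 and 4614 at f = 0.10.

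**Step 5: the second strip.** If a positive result on either strip leads to stage 2, patients who are T-positive but CC-negative are all verified. Assume that 19% of CC-negatives are T-positive (1 − 0.81, the specificity assumed in Section 2.11 for groups 2 and 3), independently of NCC. Simulation at 500 then gives about 6.6, 8.8 and 13.0 points at f = 0.50, 0.25 and 0.10, where f applies to the remaining double-negatives. The shortfall is smaller but remains.

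**Step 6: specificity.** 1.96 × √(0.99 × 0.01/400) = 0.98 points with full verification. It stays at about 1 point for every f, because specificity barely depends on the few missed cases.

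**The case against.** The best defence is that Section 2.7 is loosely worded. Its word for all may mean all patients selected for stage 2 whatever their POC result, as opposed to CC-positives only in groups 2 and 3. The sentence is careless in another respect: it cites Figure 2, a map, for group 1 and Figure 3, the group 1 flow, for groups 2 and 3, whereas Section 2.5 assigns Figures 3 and 4. This defence may be right. It would remove the contradiction, but it would confirm the two-stage design, and the sample-size point would then apply in full.

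The fraction of negatives may also be given in the flow figures, which are not shown, or in the full protocol. No omission is claimed here; the half-widths for f below 1 are therefore conditional.

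A reader might infer more than the article supports:
- **That every group 1 patient had a CT scan.** Section 2.7 says all for the doctor's examination. CT for all is at most implied by the next sentences.
- **That Section 2.5 contradicts Section 2.7 directly.** It speaks of participants in general and would be true under either reading.
- **That weighting is wrong if all were verified.** Inverse-sampling weights then equal 1 and change nothing. The weighting sentence also covers groups 2 and 3.
- **That the sensitivity estimate will be biased.** This would need weights to be misapplied or left out. Section 2.11 says that weighting was used, and nothing shows that it was done wrongly.
- **That the weights and the 5% target can never hold together.** They can for specificity. For sensitivity they can at 600 without losses if f is about 0.82 or more, a narrow case because the extra 100 patients are there to cover losses.

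**Conclusion.** The point holds in two parts. First, Section 2.7 conflicts, as written, with the abstract and the Figure 3 caption on who in group 1 was examined. Second, the stated precision for sensitivity is right at 500 evaluable patients only under full verification, which is not the design that the abstract and Figure 3 describe.

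Under the two-stage design the half-width is about 6.9 points at 50% verification of negatives, 9.5 to 9.7 at 25% and 14 to 15 at 10%, or somewhat less if T-positive, CC-negative patients are all verified. These figures rest on the plan's own sensitivity, specificity and prevalence, on assumed fractions, and on random selection of the verified negatives. The stated precision for specificity stands. This is an inconsistency and a precision claim to correct; it does not show that the estimator is invalid.

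**What to change.** 1. Reconcile Section 2.7 with the abstract and the Figure 3 caption by stating who in group 1 was examined and who was scanned.
2. Correct the figure citations in Section 2.7 to agree with Section 2.5.
3. If only a subset of POC-negatives was verified, restate in Section 2.11 the expected half-width for sensitivity, using the actual sampling fraction and saying how T-positive, CC-negative patients are handled.
4. State that the NCC cross-tabulation uses weights equal to the inverse of the sampling fraction. These equal 1 if everyone was verified, so the sentence can stand under either reading and weighting need not be dropped.

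The cost is wording, one recalculation and, if a subset was verified, a less favourable stated precision. No new patients are needed.

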**Figure 4 diagnostics-11-01528-f004:**
[figure not shown]
Flow of the diagnostic accuracy study in Tanzania for patients attending the outpatient department of district hospitals with symptoms of intestinal worm infections (group 2) and other symptoms (group 3) that were not specific neurological signs and symptoms. In this two-stage design, all patients were tested using the TS POC test (=index test; stage 1), after which all positive, and a subset of negative, patients were selected for different reference tests. Clinical examination and a brain CT scan (stage 2) were only performed on patients positive for CC on the TS POC test.

**Table 1 diagnostics-11-01528-t001:** Reference tests used to assess the sensitivity and specificity of the TS POC test for the detection of taeniosis, cysticercosis, and neurocysticercosis.

Disease Presentation	TS POC Test Strip	Purpose	Reference Standard
Taeniosis	TS POC T	Diagnosis/treatment Monitoring/surveillance Epidemiological research	copro antigen ELISA (stool ag) copro PCR (stool DNA) rES33 immunoblot (serum ab)
Cysticercosis	TS POC CC	Monitoring/surveillance Epidemiological research	EITB-LLGP (serum ab) rT24H immunoblot (serum ab) serum antigen ELISA (serum ag)
Neurocysticercosis	TS POC CC	Diagnosis/treatment and management Epidemiological research	Composite case definition according to Del Brutto et al.’s criteria [8]

TS POC T: *Taenia solium* point-of-care test taeniosis test strip; ELISA: enzyme-linked immunosorbent assay; PCR: Polymerase Chain Reaction; TS POC CC: *Taenia solium* point-of-care test cysticercosis strip; EITB: enzyme-linked immunoelectrotransfer blot; LLGP: lentil lectin-bound glycoproteins.

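### The NCC reference standard counts serum antibodies while the index strip is itself a larval-stage antibody test, so apparent NCC accuracy, chiefly sensitivity, is likely to be inflated

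*Protocol article*

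**What the plan says.** **Index test.** Section 2.1 of the protocol article describes a two-strip cassette. One strip targets the adult stage; the other is "one to detect antibodies against the larval stage of the parasite (using the recombinant CC antigen rT24H"). Table 1 assigns this second strip to both CC and NCC.

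**Reference for NCC.** Section 2.3 states: "For NCC, a composite case definition was used as the gold standard". Section 2.7 describes the criteria: "These were based on clinical symptoms, neuroimaging, the detection of antibodies and antigens in serum, and epidemiological considerations". The only absolute imaging criterion it lists is a cyst with a visible scolex. Other lesions, including parenchymal calcifications, are major or minor imaging criteria.

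**Antibody tests in the study.** Section 2.3 states: "For CC, the reference methods were the EITB-LLGP, rT24H immunoblot, and the B158/B60 monoclonal antibody-based serum antigen ELISA". The Introduction says: "For serology, the lentil lectin-bound glycoproteins-enzyme-linked immunoelectrotransfer blot (LLGP-EITB) is the test of choice". No section says which antibody test feeds the NCC composite.

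**Analysis.** Section 2.11 uses a Bayesian approach for taeniosis and CC. For NCC it cross-tabulates the strip result with the final diagnosis. Section 2.10 blinds laboratory staff to the index result, and the two CT readers to the index and reference results.

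**The concern.** A reference standard should carry information about disease that does not come from what the index test measures. Here, part of the NCC diagnosis rests on antibodies in the same patient's blood, and antibody is what the strip detects. A patient with a compatible lesion but no detectable antibody is less likely to be classed as NCC. If the strip is also negative, a missed case leaves the denominator of sensitivity.

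The analysis cannot absorb this. For taeniosis and CC the plan allows for imperfect reference tests. For NCC it treats the composite as free of error. Blinding protects each reading but does not take the antibody result out of the case definition. The Discussion covers diagnostic review bias, the subjectivity of CT and clinical findings, and delayed verification, but not this overlap.

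Table 1 gives diagnosis, treatment and management of NCC as a purpose of this strip, and the Conclusions tie the test to triage of patients. An overstated sensitivity would hide missed cases.

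**Working it through.** **1. The plan's own figure.** Inputs from section 2.11: sensitivity 93%, specificity 99%, NCC prevalence 20%, half-width 5%, 95% confidence (z = 1.96).

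- Cases needed for sensitivity: 1.96² × 0.93 × 0.07 / 0.05² = 100.03. Participants: 100.03 / 0.20 = 500.2.
- Participants needed for specificity: (1.96² × 0.99 × 0.01 / 0.05²) / 0.80 = 19.0.

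The stated 500 is reproduced and is driven by sensitivity. It does not depend on how the reference is built, so the overlap changes no stated number. It affects what the estimate means.

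**2. Simple illustration at the planned sensitivity.** Take 100 true NCC cases, of which 93 are strip-positive and 7 strip-negative. Assumption: the 7 are also negative on the serum antibody test (full concordance). Let q be the share of the 7 that fail the composite for want of the antibody criterion.

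Apparent sensitivity = 93 / (93 + 7(1 − q))

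| q | Denominator | Apparent sensitivity | Rise (points) |
|---|---|---|---|
| 25% | 98.25 | 94.7% | 1.7 |
| 50% | 96.50 | 96.4% | 3.4 |
| 75% | 94.75 | 98.2% | 5.2 |

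The rise cannot exceed 7 points. Only the last row passes the planned half-width of 5 points.

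**3. Relaxing full concordance.** Assumptions: prevalence 20%; 20% of true cases are reference-positive on imaging alone (a = 0.2); the other 80% need a positive serum antibody test (b = 0.8); 10% of non-cases have compatible lesions and become reference-positive if antibody-positive (c = 0.1). Strip and serum test have the same sensitivity (Se) and specificity (Sp). Their dependence within true cases and within non-cases is d, from 0 (independent) to 1 (maximal).

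- Both positive, among cases: p = Se² + d(Se − Se²)
- Both positive, among non-cases, with f = 1 − Sp: u = f² + d(f − f²)
- Reference-positive: R = 0.2(a + b·Se) + 0.8·c·f
- Reference-positive and strip-positive: J = 0.2(a·Se + b·p) + 0.8·c·u
- Strip-positive: I = 0.2·Se + 0.8·f
- Apparent sensitivity = J / R; apparent specificity = (1 − I − R + J) / (1 − R)

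Example with Se 93%, Sp 99%, d = 0.5: p = 0.89745, u = 0.00505, R = 0.1896, J = 0.1812, I = 0.194. Apparent sensitivity is 95.6% and apparent specificity 98.4%.

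| True Se / Sp | d | Apparent Se | Apparent Sp |
|---|---|---|---|
| 93% / 99% | 0 | 92.6% | 97.7% |
| 93% / 99% | 0.5 | 95.6% | 98.4% |
| 93% / 99% | 0.9 | 97.9% | 99.0% |
| 75% / 90% | 0 | 71.9% | 86.9% |
| 75% / 90% | 0.5 | 83.0% | 89.1% |
| 75% / 90% | 0.9 | 91.8% | 90.9% |

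If imaging alone settles every case and serology plays no part (a = 1, b = 0, c = 0), the apparent values equal the true ones.

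With dependence of 0.5 to 0.9, sensitivity rises by about 3 to 5 points from 93% and by about 8 to 17 points from 75%. With independence it falls slightly. Specificity is at or below its true value in five of the six rows.

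**The case against.** A reader might infer more than the documents support, in four ways.

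- **That sensitivity and specificity are both biased upward.** The calculation does not show this. True cases that are strip-positive but serum-negative become apparent false positives, and they pull specificity down. Its direction depends on the unknown dependence.
- **That the same rT24H antigen sits on both sides of the comparison.** The article lists the rT24H immunoblot as a reference test for CC. The NCC row of Table 1 names only the composite, and the Introduction points to the LLGP-EITB. Use of the rT24H blot in the composite is not excluded, but it is not stated.
- **That the index result is part of the reference.** It is not stated to be. The overlap runs through a shared analyte.
- **That every NCC diagnosis is exposed.** A visible scolex is an imaging finding and needs no serology. The rule that combines the criteria lies in the cited source, so the share of diagnoses that turn on antibody is unknown.

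It is also fair to say that a condensed article may leave the choice of antibody assay, or a secondary analysis, to a fuller document. That silence is not the fault raised here. What remains is what the article does state: serum antibody counts towards the diagnosis, and accuracy is a plain cross-tabulation against that diagnosis. This holds even if the LLGP-EITB is the only antibody test used.

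Finally, dropping serology altogether could misclassify non-specific lesions such as calcifications. That argues against making a serology-free reference the sole basis of the NCC claim. It does not argue against reporting one alongside.

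**Conclusion.** The concern holds in a limited form. For diagnoses that imaging alone does not settle, the NCC reference depends partly on the analyte that the strip measures, and none of the stated safeguards removes this. Apparent NCC accuracy, chiefly sensitivity, is likely to be inflated, provided that the strip and the serum antibody test are positively correlated. Such correlation is to be expected when both detect larval-stage antibodies in the same patient, but the article gives no estimate of it. The direction for specificity is uncertain.

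The size cannot be derived from the documents. At the planned 93%, both illustrations put the rise at about 2 to 5 points, under the assumptions stated with each. It would be larger if the true sensitivity were lower, and nil where imaging decides. The overlap itself is certain from the text; the amount of inflation is not.

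**What to change.** - **Section 2.7:** name the antibody test that enters the NCC composite and exclude the rT24H immunoblot from it. Keep the published composite as the main reference.
- **Section 2.11:** add a pre-specified, co-reported analysis of NCC accuracy against a classification without serum antibodies, built from the blinded CT readings plus clinical and epidemiological criteria. Show imaging-definite cases separately.

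**Cost.** One extra classification from data already recorded, with no new patients or tests. The added analysis will carry some misclassification of non-specific lesions, so it should be read beside the composite and not in place of it. The reported sensitivity may be lower.
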